## Abstract

**Background:**

There is a growing recognition of the key role of the therapeutic relationship in the outcomes of psychotherapy. However, current understanding of its specific components, their interplay and related patient-therapist dynamics is limited.

**Objective:**

(a) To validate two self-report measures to assess subjective affective reactions of patients toward their psychotherapists during specific therapy sessions, and (b) to explore the relationships and dynamics among four elements of the therapeutic relationship: patient reactions toward the therapist, working alliance, alliance ruptures and repairs, and the real relationship.

**Methods:**

This study uses a nonrandomized, two-time point longitudinal design. The target population is adult patients currently engaged in individual psychotherapy for heterogeneous mental conditions. Participants are recruited through two online recruitment platforms: Research for Me and ResearchMatch. Data collection involves administering two surveys through the Qualtrics online survey platform. The baseline survey assesses information about the most recent therapy session and the preceding week, while the follow-up survey collects data on the subsequent therapy session and the days leading up to it.

**Discussion:**

This research offers three main contributions: (a) it furthers evidence-based assessment in psychotherapy by creating and validating two novel, succinct self-report tools; (b) it enhances theoretical understanding within therapeutic relationship research by exploring the significant impact of patients' perceptions of relationship elements on session outcomes variability; and (c) it will identify therapeutic relationship elements that can either enhance or hinder the overall relationship quality and session outcomes.

**Ethics and dissemination:**

The study protocol was approved by the Institutional Review Board of the University of North Carolina at Chapel Hill. The results will be published in indexed peer-reviewed journals and presented at relevant psychology and psychiatry conferences.

## Background and rationale

The therapeutic relationship between patients and therapists plays a crucial role in the unfolding of the psychotherapy process and contributes significantly to the treatment outcomes, regardless of the therapeutic techniques and models used (
Gelso, 2018;
Norcross & Lambert, 2018). Growing empirical evidence emphasizes the therapeutic relationship, pointing to the theoretical and clinical importance of broadening the investigation to underexplored or unexplored aspects of this crucial relationship (
Bhatia & Gelso, 2018). Such a valuable shift from a broad analysis of the general therapeutic relationship to a more focused investigation of its specific components, as well as their interplay and their relationships with patient, therapist, and treatment variables, will improve our understanding of the psychotherapeutic relationship.

Among the patient’s characteristics, the mediating role of personality traits in shaping the therapeutic relationship appears particularly intriguing, although it is not yet fully understood (
Dennhag *et al.*, 2017;
Fletcher & Delgadillo, 2022). Furthermore, although evidence emphasizes the influence of both patient and therapist contributions to the therapeutic relationship (
Norcross & Lambert, 2019;
Wampold & Imel, 2015), the existing literature focuses mainly on therapist variables, often neglecting the patient’s unique perspective, especially with respect to their affective and cognitive responses during sessions (
Norcross & Lambert, 2018). This is noteworthy because among the emotions experienced by patients in the “here and now” of the therapeutic session, those directed at the therapist are particularly significant and valuable for the fulfillment and facilitation of the therapeutic work in question (
Høglend, 2014;
Subic-Wrana *et al.*, 2016).

Interestingly, although various measures have been developed to assess emotions (
Norcross & Lambert, 2019;
Peluso & Freund, 2018), only a few of them explicitly incorporate specific attention to affective processes within the dyadic therapeutic relationship (
Stefana *et al.*, 2023a). Existing self-report measures that capture therapeutic relationship constructs such as alliance (
Wampold & Flückiger, 2023) only indirectly address affective content. Therefore, it would be valuable to have scales optimized to focus on affect in the context of ongoing therapy.

### Study objectives

This study has two primary objectives:

a. To validate the
*in-Session Patient Affective Reactions Questionnaire* (SPARQ) and the
*Rift In Session Questionnaire* (RISQ) devised by
Stefana *et al.* (2023b). These self-report measures assess the subjective affective reactions of patients toward their psychotherapists during specific therapy sessions. The study aims to establish the reliability and validity of these measures through a rigorous psychometric evaluation.b. To explore the relationships and dynamics among four elements of the therapeutic relationship: patient reactions toward the therapist, working alliance, alliance ruptures and repairs, and the real relationship. The study aims to investigate how these elements interrelate and how they collectively influence the outcomes of the therapy session, from the patient’s perspective. Furthermore, the study aims to examine possible moderating effects of patient, therapist, and process characteristics on the strength of the therapeutic relationship and the outcome of the session.

## Methods

### Study design

This study employed a nonrandomized, two-time point longitudinal design. The study started in March 2023 and is ongoing. The initial development of the scales in
Stefana *et al.* (2023b) used a large initial item pool and a large, single administration sample to generate adequate sample size to use exploratory and confirmatory factor analysis and item response theory to guide item selection. A limitation of that work was that the SPARQ and RISQ items were originally embedded in a larger item pool. It is possible that the items would perform differently in the shorter, extracted format that would be more useful in clinical practice and therapy research. A second limitation is that each participant responded only once, so it was not possible to estimate score stability or sensitivity to change. The approach used in the present study addresses both limitations of the prior work: (a) it collects cross-sectional data for the validation of the SPARQ and the RISQ in the extracted, brief item sets, and (b) gathers longitudinal data to examine how specific elements of the therapeutic relationship are related to each other and to the outcome of the therapy session, from the perspective of patients. Furthermore, it allows us to test the moderating role of personality characteristics of the patients.

### Participants

This research focuses on adults (18 years and above) receiving individual psychotherapy for a range of mental health conditions, without limiting the type of mental disorder. Participants must be fluent in English and capable of providing informed consent.

Participants are recruited through two online recruitment platforms: Research for Me and ResearchMatch. Research for Me has approximately 12,000 registered volunteers in North Carolina, while ResearchMatch (
Harris *et al.*, 2012) provides access to more than 155,000 volunteers across the United States. These platforms connect researchers with individuals interested in contributing to scientific advancements in various fields. The use of the extensive reach and user-friendly interfaces of Research for Me and ResearchMatch improves participant recruitment for this study, ensuring a representative sample from diverse backgrounds and geographic locations.

### Sample size estimation

The study includes two main goals, and the necessary sample size varies accordingly.

The first goal is validation of the psychometrics of the SPARQ and RISQ in their brief, extracted item sets. Based on the number of items in the measures to be validated (
*k* = 8 for the SPARQ and
*k* = 4 for the RISQ), as well as the expected moderate to strong factor loadings (as found in the embedded format study;
Stefana *et al.*, 2023b), a sample size of
*N* = 315 is recommended (
Dimitrov, 2012). This sample size also accounts for the complexities of a two-factor model which includes non-normal indicators and potential missing values (
Dimitrov, 2012). However, we anticipate recruiting at ~700 participants. The sample size considered for this study is deemed feasible based on the previous psychotherapy-related study of our team that successfully used the same two online recruitment platforms.

For the second goal, evaluating prospective associations among scores rated over the course of treatment, and the potential moderating effects of personality, even using conservative estimates that only 70% of cases would complete the follow-up ratings, power would be 80% to detect effects as small as
*f
^2^
* = .02 (alpha = .01, two-tailed,
*N* = 500, and including up to 9 predictors or covariates) (
Faul *et al.*, 2009), corresponding to a small effect size using Cohen’s (
Cohen, 2013) benchmarks.

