### Data form domain

**
*Sociodemographic, Clinical, and Treatment Data Form.*
** This form captures self-reported information on the patient’s age, biological sex, gender identity, educational background, ethnicity, any existing psychiatric diagnoses, and the duration and frequency of the current psychotherapeutic intervention. It also records the modality of session attendance (i.e., in-person, video call, or telephone call), the setting of therapy (for example, private practice, private healthcare institution, university counseling center), and the biological sex of the therapist. Information about the specific types of psychotherapy that participants were undergoing was not gathered.

**
*Personality domain.*
** The
*Big Five Inventory–2-Extra-Short form* (BFI-2-XS) (
Soto & John, 2017) is a concise 15-item self-report instrument that captures personality at the level of the Big Five domains. Each domain is represented by three items, and each item is rated on a 5-point Likert scale. The five domains include extraversion, agreeableness, conscientiousness, negative emotionality (also referred to as neuroticism), and open-mindedness. The average alpha reliability for the BFI-2-XS domain scales fell between .61 and .63, with the total range extending from .51 to .72. Test-retest reliabilities for these scales averaged .70 in the university sample (ranging from .60 to .80) and .76 in the college sample (with a range of .71 to .80).

The
*Level of Personality Functioning Scale-Brief Form 2.0* (LPFS-BF 2.0) (
Weekers *et al.,* 2019) is a 12-item self-report questionnaire used to assess the severity of personality pathology. It measures impairment in self-functioning and interpersonal functioning based on levels of personality functioning according to the DSM-5. Cronbach’s alpha for the LPFS-BF 2.0 was .82 for the total scale, .79 for the self-functioning scale, and .71 for the interpersonal functioning scale.

**
*Mental health state domain.*
** The
*International Positive and Negative Affect Schedule–Short Form* (I-PANAS-SF) (
Thompson, 2007) is a 10-item self-report measure that captures the frequency of positive and negative affects experienced over the past week. It provides an understanding of the emotional states of the patients. The I-PANAS-SF positive affects and negative affects subscales showed Cronbach’s alphas of, respectively, .78 and .76.

The
*Patient Health Questionnaire–9* (PHQ-9) (

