### Data analysis

Regarding the first objective, the analysis plan for validating the two scales includes several statistical techniques to evaluate the psychometric properties. In the initial stage, will be used to evaluate the suitability of the proposed factor models on the complete sample of participants. These will use the same analytic methods used in the original scale development, but with the extracted, short-form subset of items (versus the prior work, where these items were embedded in the larger original item set). Specifically, a two-factor model representing positive affect and negative affect will be tested for the SPARQ, while a single-factor model will be applied to the RISQ (
Stefana *et al.*, 2023b). Item response theory (IRT) models will be used to analyze the options characteristics of each scale and obtain detailed information at the item level (including item difficulty, discrimination, and category functioning). In addition to these specific analyzes, several statistical procedures will be conducted to evaluate the psychometric properties of the scales. Internal consistency will be assessed using Cronbach’s alpha (for comparability with what is most often reported for other scales), McDonald’s omega total coefficients (which is more appropriate for measures that include more than one factor), and average inter-item
*r* (which avoids confounding internal consistency and scale length, which is a well-known limitation of Cronbach’s alpha;
Streiner *et al.*, 2015).

Criterion validity will be examined by calculating the correlations between the scales and various external variables, including sociodemographic, clinical, and treatment variables. Validated measures of traits, mental state characteristics, specific elements of the therapeutic relationship, and session outcomes will also be included in the analysis. Fisher’s z transformation will be used to average pooled correlation matrices, providing descriptive summaries for associations with sets of variables.

Regarding the second aim, correlations will quantify the pre-post stability of the repeated measures. The PROCESS macros will test for mediation of pre-post symptom severity, psychosocial functioning, and quality of life by ratings of the client-therapist relationship, affect, and working alliance, as well as the extent to which these might show moderated mediation due to demographic or personality variables (

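### The stated 80% power at f² = .02 for Aim 2 does not reproduce: one coefficient has about 71–72%, and the planned indirect effects can do no better and may do much worse

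*Protocol article*

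**What the plan says.** Protocol article, Sample size estimation, treats the second goal as "evaluating prospective associations among scores rated over the course of treatment, and the potential moderating effects of personality". It states that, "even using conservative estimates that only 70% of cases would complete the follow-up ratings", the "power would be 80% to detect effects as small as" f² = .02, with alpha .01 two-tailed and N = "500, and including up to 9 predictors or covariates". It identifies that value with a small effect on Cohen's benchmarks. For the first goal, the same section says "we anticipate recruiting at ~700 participants".

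Under Data analysis, the tests for the second aim are stability correlations, then mediation models run with the PROCESS macros, "as well as the extent to which these might show moderated mediation due to demographic or personality variables". Alpha is again .01, two-tailed. The article gives no power for an indirect or conditional indirect effect and no assumed path sizes.

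**The concern.** One power figure is offered for the second aim, so it should follow from the inputs printed beside it and describe the tests that will be run. It appears to do neither. The inputs fit a test of a single coefficient, for which 80% looks too high. An indirect effect is a product of two paths, and its power is not that of one coefficient.

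What is at stake is how null results are read. The article's section on minimizing bias presents the sample size work as protection against under-powered analyses. A reader who accepts this would take a null moderation or mediation result as having had an 80% chance of showing an effect of f² = .02. On the article's own inputs it did not.

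**Working it through.** **Inputs.** From Sample size estimation: f² = .02, alpha = .01 two-tailed, N = 500, up to 9 predictors, about 700 recruited, 70% completing follow-up. From Data analysis: mediation and moderated mediation at alpha .01 two-tailed. From the measures sections, used only in step 4: mean alphas of .61 to .63 for the BFI-2-XS domains, .82 for the LPFS-BF 2.0 total, .74 for SPARQ negative affect, and .91 for the WAI-SR total (lower of the two values given).

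**Step 1: the stated figure.** For one coefficient among k = 9 predictors, the test is a t test with N − k − 1 degrees of freedom and noncentrality √(f² × N).

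- N = 500: noncentrality √(.02 × 500) = √10 = 3.162, df = 490, two-sided power **71.8%**.
- Completers implied by the article: .70 × 700 = 490. Noncentrality √(.02 × 490) = √9.8 = 3.130, two-sided power **70.7%**.

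Other readings of the inputs:

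| Test at f² = .02, N = 500 | Power |
|---|---|
| One coefficient, alpha .01, two-sided | 71.8% |
| One coefficient, alpha .01, one-sided | 79.6% |
| One coefficient, alpha .05, two-sided | 88.4% |
| Omnibus F test of 9 predictors, alpha .01 | 31.5% |

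Only the one-sided test gives about 80%, and the article says two-tailed. The number of predictors hardly matters: with one predictor the two-sided figure is still 71.8%.

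**Step 2: what gives 80% two-sided.** The detectable f² is .0235 at N = 500 and .0240 at N = 490. At f² = .02, 588 completers are needed, or 588 / .70 = 840 recruited.

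**Step 3: indirect effects.** The joint-significance test declares an indirect effect only if both paths are significant. Its power is about power(a) × power(b), and so cannot exceed the power of the weaker path. The article gives no path sizes, so these are assumptions:

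| f² of the two paths | N = 490 | N = 500 |
|---|---|---|
| .02 and .02 | .7067² = 50% | .7176² = 51.5% |
| .02 and .05 | .7067 × √.9817 = 70% | .7176 × √.9840 = 71% |
| .03 and .03 | 79.8% | 81.1% |

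A simulation of the first row at N = 500 with a 99% percentile bootstrap (600 trials) gave about 47%. With both paths at .02, joint-significance power of 80% needs about 736 completers. The same product and the same ceiling apply to a conditional indirect effect, with the interaction coefficient as one of the two paths.

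**Step 4: sensitivity to scale reliability, only if f² = .02 is a true-score effect.** For centred, uncorrelated scores, the observed interaction f² is about .02 × (moderator reliability) × (predictor reliability). At N = 490:

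- BFI-2-XS (.62, the midpoint of .61 and .63) with SPARQ negative affect: .02 × .62 × .74 = .0092, power 32%.
- BFI-2-XS with WAI-SR: .02 × .62 × .91 = .0113, power 41%.
- LPFS-BF 2.0 with WAI-SR: .02 × .82 × .91 = .0149, power 55%.

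**The case against.** Four points can be made for the article.

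First, .0235 rounds to .02 at two decimals, so the authors may have rounded a correctly computed detectable effect. That would explain the figure but not rescue it. The text ties .02 to Cohen's small-effect benchmark, so it reads as the value itself, and at that value power is 71–72%.

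Second, a continuous moderator enters as one product term, so a single-coefficient test is the right one for moderation. This stands. The moderation claim fails because the number does not reproduce, not because the formula is wrong for it.

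Third, the power sentence names prospective associations and moderation, not indirect effects, and an article may leave indirect-effect power to a fuller document. A reader might infer that the article claims 80% power for mediation by name; it does not. What remains is that this is the only figure given for an aim whose named tests include mediation and moderated mediation, and it does not carry over to them.

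Fourth, the reliabilities. From "The average alpha reliability for the BFI-2-XS domain scales fell between .61 and .63" a reader might infer that the study is more likely to miss personality moderation than to find it. The documents do not support that. They never call f² = .02 a true-score effect, and if it is the observed effect, attenuation is already in it. Even on the true-score reading, LPFS-BF 2.0 with WAI-SR has about 55%, and the section also gives BFI-2-XS test-retest averages of .70 and .76, higher than the mean alphas.

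**Conclusion.** The stated 80% is wrong for the inputs given. For one coefficient, including a product term, power is about 72% at N = 500 and 71% at the 490 completers that 70% of 700 implies. That is a shortfall of 8 to 9 percentage points. It rests only on reading the figure as a single-coefficient test. The article does not name the test, but this reading is far closer to its figure than the omnibus alternative.

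For mediation and moderated mediation the ceiling is firm and the exact size is not. By joint significance, power cannot exceed 71–72% if the weaker path is f² = .02. It is about 50% if both paths are .02, and 80% needs about f² = .03 on each. Attenuation from unreliable scales is a conditional sensitivity figure and not part of the conclusion.

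**What to change.** In Sample size estimation, restate single-coefficient power as about 71–72% at f² = .02, or 80% at f² of about .024, and use 490 completers or explain the 500. Name the test. Add a separate power figure or detectable effect for the indirect and conditional indirect effects, with the path sizes and the method of testing stated. Align the claim about under-powered analyses in the bias section with these figures. In reports, do not describe a null mediation or moderation result as 80% powered at f² = .02.

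A reliability-adjusted figure for the product terms may be added, labelled as applying only if f² is a true-score effect.

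The article's Study status section says data collection is complete, so the sample is fixed and this is a correction of wording and interpretation. The cost is a few recalculated, less favourable numbers.

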Eubanks *et al.*, 2018). A rupture is considered repaired or resolved when the patient and therapist successfully reestablish their collaborative efforts in therapy and reinforce their emotional connection. The part B of the PSQ includes an initial item that investigates the presence (“Yes” or “No”) of any tension, conflict, or misunderstanding in the therapist-client relationship during the session. If such an event occurred, it is followed by three items that gauge the peak intensity of the tension, the degree to which the problem was addressed in that session, and the patient’s perception of the solution of the problem by the end of the session.

The
*in-Session Patient Affective Reactions Questionnaire* (SPARQ) (
Stefana *et al.*, 2023b) is a patient-reported tool that comprises 8 items that explore the patterns of thought, feeling, and behavior activated and experienced by the patients toward their therapist during a session. It consists of two scales: Positive Affect and Negative Affect. The positive affect scale exhibited a Cronbach’s alpha coefficient of .86 and an average inter-item correlation of .61. On the other hand, the negative affect scale demonstrated an alpha of .74 and an average inter-item correlation of .41.

The
*Rift In-Session Questionnaire* (RISQ) (
Stefana *et al.*, 2023b) is a 4-item self-report questionnaire designed to measure the patient’s risk of experiencing ruptures in the therapeutic relationship. The RISQ measures feelings of belittlement, rejection, disparagement, and attack. The RISQ demonstrated good internal consistency with a Cronbach’s alpha coefficient of .75 and an average inter-item correlation of .43.

**
*Session outcome domain.*
** The
*Session Evaluation Scale* (SES) (
Lent *et al.*, 2006), part of the Helping Skills Measure (
Hill & Kellems, 2002), evaluates the quality of the therapy session from the patient’s perspective. It consists of five items, four of which are rated on a 5-point Likert scale, and the fifth item gauges the effectiveness of the session. The 5-item SES showed a Cronbach’s alpha coefficients ranging from .88 to .89 (
Lent *et al.*, 2006).

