Hayes, 2022). Given the number of analyses, alpha will be .01, two-tailed.

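### The 80% power stated for the second aim does not follow from its own inputs: f² = .02 at two-tailed alpha .01 with N = 500 gives about 72%

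*Protocol article*

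**What the plan says.** The Sample size estimation section of the protocol article treats the two aims separately. For the second aim (prospective associations and moderation by personality) it gives a full power statement: "only 70% of cases would complete the follow-up ratings, power would be 80% to detect effects as small as" f² = .02. The conditions follow in brackets: "alpha = .01, two-tailed", N = 500, "and including up to 9 predictors or covariates". It calls this a small effect on the usual benchmarks. On recruitment the same section says "However, we anticipate recruiting at ~700 participants".

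The Data analysis section repeats the error rate and the sidedness for the tests themselves: "Given the number of analyses, alpha will be .01, two-tailed". No one-tailed test is mentioned anywhere in the article.

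**The concern.** Every quantity needed to check the power figure is printed: effect size, alpha, sidedness, sample size and number of predictors. This is therefore not a detail left to a fuller plan. The parts of the statement either agree or they do not.

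They do not agree, and the printed power is too high for the printed test. The section on efforts to minimise bias counts the sample size calculation among its safeguards against underpowered analyses. A reader who meets a null moderation or prospective result would naturally use the printed figure to judge how firmly an effect of f² = .02 has been ruled out.

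**Working it through.** **Inputs**, all from Sample size estimation: f² = .02; alpha = .01, two-tailed (confirmed in Data analysis); N = 500; 9 predictors; stated power 80%.

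**Model.** Test of one coefficient in a multiple regression:
- error df = N − 9 − 1 = 490
- noncentrality λ = f² × N = .02 × 500 = 10, so on the t scale √10 = 3.162

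**Attempt to reproduce 80% as written (two-tailed .01).**
- Normal approximation: Φ(3.162 − 2.576) = Φ(0.586) = 72.1%
- Exact, noncentral F with 1 and 490 df: **71.8%**

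The stated figure is not reproduced. The gap is about 8 percentage points, and the type II error is 100 − 71.8 = 28.2% against the stated 20%.

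**Does another reasonable calculation of the same two-tailed test reach 80%?**
- 1, 9 or 10 predictors: 71.8% in each case, so the covariate count hardly matters
- .02 read as R², so f² = .02/.98 = .0204: 72.8%
- Correlation test by Fisher's z: 71.4% to 72.5%
- 490 completers (.70 × 700): 70.7%

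None does. With N = 500 and f² = .02, two-tailed power of 80% would need alpha of about .021.

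**What would give about 80%?**
1. *One-tailed .01, other inputs unchanged.* Normal approximation Φ(3.162 − 2.326) = Φ(0.836) = 79.8%; exact 79.6%.
2. *Two-tailed .01, power fixed at 80%, solved for f².* The result is f² = .0235 at N = 500 and .0240 at N = 490. Both become .02 when rounded to two decimals.

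Two decimals are too coarse for this purpose. At N = 500, two-tailed power is 56.1% at f² = .015 and 82.7% at f² = .0249, and both ends of that range would be printed as .02.

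**What 80% at exactly f² = .02 would require (two-tailed .01):** 588 completers, or 588/.70 = 840 recruited at 70% completion.

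**The case against.** The strongest defence is that the sentence has the form of a sensitivity statement: power is fixed at 80% and the smallest detectable effect is the output. On that reading every stated input is kept, the output is .0235, and the only flaw is rounding. The practical gap is then .0235 against .02, both near the small-effect benchmark. Data collection is also complete according to the Study status section, so no enrolment decision depends on the figure. Much of this stands, and it limits how serious the point is. It does not make the sentence right, because a detectable effect rounded down overstates what the study can detect. At the printed .02 the power is 72%.

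Some stronger readings are tempting but not supported:
- *A one-tailed calculation was mislabelled as two-tailed.* A reader might infer this from the 79.6%. Rounding explains the figure equally well, and the article does not show the calculation.
- *N = 500 is itself an error.* 70% of exactly 700 is 490, but recruitment is given only as approximately 700, and 500/.70 is about 714. The difference costs about 1 point of power.
- *Power is really about 31%.* That is the joint test of all 9 predictors (31.5%). A statement described as two-tailed, about predictors or covariates and moderating effects, fits a single coefficient and does not claim to power a 9-df F test.
- *The figure fails for the rupture-repair items of the Patient Session Questionnaire.* Those items are asked only after a reported rupture, but the sample size section does not say its figure covers them. The article gives no rupture rate from which to compute their power.

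**Conclusion.** The stated power is wrong as written. Under two-tailed alpha .01, N = 500 and f² = .02, power for a single coefficient is about 72% (about 71% with 490 completers), not 80%. Put the other way, 80% power is reached at f² of about .0235 to .024, roughly a fifth larger than the stated .02 (.0235/.02 = 1.18; .0240/.02 = 1.20). The origin of the 80% cannot be settled from the article, and the correction does not depend on it.

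The result assumes a one-coefficient test in a linear regression, the reading most favourable to the plan. It does not extend to the indirect effects in the planned mediation and moderated-mediation analyses.

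The consequence is moderate. A reader might conclude that the second aim is seriously underpowered or the design invalid, but the shift in detectable effect is too small to support that. No analysis, alpha level or objective has to change.

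**What to change.** Replace the power sentence with one whose parts agree and which names the test, for example:

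*With about 500 completers, two-tailed alpha .01 and a test of a single coefficient in a model with up to 9 predictors, power is 80% for f² of about .024 and about 72% for f² = .02.*

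Give f² to three decimals. As follow-up is finished, put in the actual number of completers and recompute both figures; with 490 they would be f² = .024 and 71%.

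The cost is one reworded sentence and a slightly less favourable figure. No further enrolment and no change to the analyses is needed.
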